## Abstract

**Background:**

Repeated or chronic stress is considered a major source of disease, in terms of both somatic and mental illnesses. The prevention of stress-related disease by interventions for relaxation has thus increased societal relevance. In this randomized controlled non-inferiority trial, we will compare a newly developed virtual reality (VR) environment for relaxation to an active control group applying a freely chosen relaxation method. To test if our VR environment supports relaxation in a situation of acute stress, a standardized stress induction protocol will precede the relaxation phase.

**Methods:**

One hundred healthy participants will be recruited from the University of Siegen and randomly assigned to the VR or the active control group that will be free to choose their own relaxation strategy. The multi-sensory VR includes visual, acoustic, and haptic features to induce a strong feeling of presence. The laboratory testing will comprise a baseline measurement, a stress induction, a relaxation intervention, and a recovery measurement. The primary outcomes are self-reported stress and relaxation measured with a visual analog scale (VAS) at pre- and post-baseline, at the start, middle, and end of the stress induction, at pre- and post-relaxation, at pre- and post-recovery, and in the evening of testing. Secondary outcomes are the physiological parameters, namely heart rate and heart rate variability, tonic skin conductance level as well as the number of non-specific skin conductance responses, systolic and diastolic blood pressure and respiratory rate recorded during the four experimental phases as well as state mood, and state rumination assessed at four time points (pre- and post-stress, post-relaxation, and in the evening of testing). Finally, post-event processing will be assessed after relaxation and in the evening of testing. Repeated measures ANOVAs will be performed to test for statistical effects of group, time, and group × time interaction.

**Discussion:**

The newly developed, multi-sensory VR offers an intervention for relaxation without prior training. Its immersive character might increase efficacy compared to other relaxation methods, especially in situations of acute stress. Future directions could be the development of a mobile version of the VR to enhance accessibility for users. To achieve a transfer of training effects to real life, VR components should successively be eliminated until relaxation is practiced without guidance by the VR.

**Trial registration:**

ISRCTN Registry ISRCTN11162338. Retrospectively registered on January 22, 2021

## Administrative information

Note: The numbers in curly brackets in this protocol refer to SPIRIT checklist item numbers. The order of the items has been modified to group similar items (see http://www.equator-network.org/reporting-guidelines/spirit-2013-statement-defining-standard-protocol-items-for-clinical-trials/).

## **Introduction**

### Background and rationale {6a}

Repeated or chronic stress is considered a major source of disease, in terms of both somatic and mental illnesses [1]. Stress-related mental disorders do not only lead to subjective suffering but are associated with large economic costs due to health care expenditures, absenteeism, and inability to work [2, 3]. The prevention of stress-related diseases by methods of stress reduction and relaxation techniques has thus an increasing societal relevance. Common relaxation practices, like mindfulness-based stress reduction and meditation techniques, achieve small to moderate efficacy rates [4–6]. They require repeated practice and the capacity to retrieve and apply them in situations of high distress.

Emerging computational power and advances in techniques have rendered the use of virtual realities (VRs) accessible and VRs increasingly immersive [7]. A VR is a 3D simulation of a natural environment that participants can explore by looking or even moving around. New VR systems with a high resolution, a broad field of view, head tracking, and stereo sounds achieve a high level of immersion, i.e., they enable natural sensorimotor perceptions in the VR. They thus have the potential to induce a strong feeling of presence and to shield participants’ attention from distraction [8]. VRs are increasingly used in the field of clinical psychology and behavioral medicine [9, 10]. Applications range from exposure therapy in patients with anxiety disorders, to addiction-related interventions to practices for mindfulness [8–12]. Within the VR, participants can find themselves in a safe space wherein they can practice a specific behavior. An advantage is that a multi-sensory VR for stress reduction does not require prior training but directly targets the process level and could train participants’ relaxation ability online.

A VR can target relaxation processes by different mechanisms. In biofeedback, training participants receive online feedback on their physiological responses (e.g., heart rate variability) to learn how to regulate those bodily stress responses [13–16]. Another way VRs can target relaxation processes is by supporting the practice of mindfulness [8, 12, 17]. VRs of this type often use nature scenes combined with nature sounds as a setting [8, 12, 16, 18, 19]. In addition, the feeling of presence generated by the VR could facilitate practicing state awareness, a basic element of mindfulness [8, 12]. In addition, VRs can also serve emotion regulation by distraction which can reduce symptoms of anxiety, depression, fatigue, and pain [20].

Significant effects of VR relaxation interventions have predominantly been found in the domain of self-reported emotional states and less so in physiological measures [16, 19, 21]. VR relaxation interventions led to reduced subjective stress [16], anxiety, and depression [15, 20, 21], as well as reduced negative affect [8, 18, 19], increased state relaxation [8, 21] and relaxation self-efficacy [13], increased recreation [19], and enhanced positive affect [12, 19].

In the current randomized controlled non-inferiority trial, we will test a newly developed VR for relaxation against an active control group applying a freely chosen relaxation method. We hypothesize non-inferiority of the VR, assuming that the VR is equally effective as a freely chosen, preferred, and well-practiced relaxation method. So far, the majority of studies evaluated the respective relaxation intervention in a calm and comforting setting. This raises the question, if participants will be capable to use the respective relaxation intervention also in stressful situations, when the intervention would be most needed and processing resources are limited. We therefore implement the VR not only for relaxation but to downregulate stress induced before the relaxation phase.

### Objectives {7}

Our main objective is to investigate if the VR intervention is non-inferior to an active control group, applying a freely chosen relaxation method, in inducing stress reduction and relaxation indicated by ratings and physiological measures.

### Trial design {8}

In the current non-inferiority trial, a randomized controlled design is applied, wherein participants will be randomly assigned to one of two parallel groups: either the virtual reality intervention (VR) or an active control group. The allocation ratio will be 1:1. To test the effect of stress reduction, stress will be induced before the relaxation phase (see the description of the procedure for more details).

## Methods: participants, interventions, and outcomes

### Study setting {9}

Data collection will take place at the University of Siegen (Germany) in the laboratories of the Department of Clinical Psychology and Psychotherapy.

### Eligibility criteria {10}

We will recruit participants aged 18 to 30 years. The eligibility criteria will be no current psychiatric or cardiovascular disease and no current intake of psychoactive or neuroactive medication. Furthermore, participants should not have experienced a trauma that could possibly be reactivated by the negative images that will be shown in the stress task

### Who will take informed consent? {26a}

Informed written consent will be obtained by the responsible experimenter of the trial management group.

### Additional consent provisions for collection and use of participant data and biological specimens {26b}

Participant data will not be used in ancillary studies. This trial does not involve collecting biological specimens for storage.

### Interventions

#### Explanation for the choice of comparators {6b}

As a comparator, we want to use a strategy for relaxation that is subjectively perceived as most effective. The active control group will be free to choose their own method for relaxation that can be conducted in a sitting position and involves low levels of physical activity. The comparator is not associated with any risks for the participants.

#### Intervention description {11a}

##### Procedure

Study participation will consist of an online pre-intervention and an online post-intervention survey taking approximately 2 h in total and one laboratory testing of approximately 1.5 h. Online surveys were set up in the online survey tool lime survey (LimeSurvey GmbH, Hamburg, Germany). The pre-intervention survey will assess chronic stress (TICS, [22]), depression, anxiety, and stress (DASS, [23]) as well as trait rumination (RSQ, [24–26]). Testing sessions will take place in the laboratories of the Department of Clinical Psychology and Psychotherapy at the University of Siegen. At the beginning of the testing session, participants will give their informed written consent and will fill out questionnaires on a computer for approximately 30 min. These questionnaires assess perceived stress (PSS-10, [27]), self-efficacy (SWE, [28]), and mindful attention and awareness (MAAS, [29]). The testing session will comprise an initial 5-min baseline measurement, a 5.5-min stress induction by the Mannheim Multicomponent Stress Test (MMST, [30]), subsequently a 15-min relaxation phase, and finally a 5-min recovery measurement. During all of these phases, physiological data will be recorded, namely an electrocardiogram (ECG), galvanic skin conductance response (GSR), respiration, and blood pressure (see description on data collection and management, SPIRIT item 18a for more details). Stress and relaxation ratings will be measured with a visual analog scale (VAS) on a Likert scale ranging from 0 (not stressed, not relaxed) to 9 (very stressed, very relaxed) at pre- and post-baseline; at the start, middle, and end of the stress induction; at pre- and post-relaxation; at pre- and post-recovery; and in the evening of testing. Additionally, two questionnaires on state mood (MDBF, [31, 32]) and state rumination (RSQs, adaptation of RSQ for state [24–26]) will be repeatedly administered at post-baseline, post-stress, and post-relaxation as well as in the evening of testing. Post-event processing (PEPR, translated to German, [33]) will be assessed after relaxation and in the evening of testing. Experienced sense of presence in the VR will be assessed directly after relaxation [34]. Figure 1 shows the procedure for the laboratory testing session.

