### Outcomes {12}

The primary outcomes are self-reported stress and relaxation measured with a visual analog scale (VAS) at pre- and post-baseline (t2); at the start, middle, and end of the stress induction (t3); at pre- and post-relaxation (t4); at pre- and post-recovery (t5); and in the evening of testing (t6). Secondary outcomes are the physiological parameters, namely heart rate and heart rate variability, tonic skin conductance level as well as the number of non-specific skin conductance responses, systolic and diastolic blood pressure and respiratory rate recorded during the four experimental phases at time points t2 to t5 as well as state mood, and state rumination assessed at four time points (at t2 baseline/pre-stress, at t3 post-stress, at t4 post-relaxation, and at t6 in the evening of testing). Finally, post-event processing will be assessed at t5 after relaxation and at t6 in the evening of testing

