### Statistical methods

#### Statistical methods for primary and secondary outcomes {20a}

Analysis of acquired raw data will be conducted in Matlab 2020b (the Mathworks Inc., Natick, MA, USA). All physiological data will be visually screened. ECG data will be analyzed with the Pan-Tompkins algorithm for QRS detection [38, 39]. Heart rate will be estimated as the number of beats per minute. Heart rate variability will be estimated using root mean square of successive differences (RMSSD, [40]). The tonic skin conductance level and the number of non-specific phasic skin conductance responses will be estimated using the matlab toolbox Ledalab [41]. Respiratory rate will be estimated per minute using a custom-made matlab script that band pass filters the data to frequencies of 0.05 to 1 Hz before detection of inhalation peaks and exhalation troughs. SPSS Statistics 27 for Windows (Armonk, NY: IBM Corp.) will be used for statistical analyses. To test the effects of time (within-subject factor), group (between-subject factor), and the time by group interaction, repeated measures ANOVAs will be performed. Additional two sample *t* tests will evaluate the group differences at relaxation and post-relaxation.

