#### Methods for additional analyses (e.g., subgroup analyses) {20b}

To explore if the current stress level, trait mindfulness, and trait self-efficacy impact the success of the applied relaxation method, we will include them as covariates in the above models. No additional subgroup or adjusted analyses are planned.

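### Post-event processing has no pre-relaxation value, and its main analysis uses neither rumination measure collected beforehand: a modest, avoidable loss of precision in one secondary outcome

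*Protocol article*

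**What the plan says.** **Outcome.** The Procedure section states: "Post-event processing (PEPR, translated to German, [33]) will be assessed after relaxation and in the evening of testing". Outcomes {12} lists it among the secondary outcomes: "post-event processing will be assessed at t5 after relaxation and at t6 in the evening of testing". Table 1 marks the first assessment at t4 rather than t5. Both follow relaxation, so no pre-relaxation value exists on either reading.

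**Related measures taken earlier.** The online survey at t1 includes trait rumination (RSQ): "The pre-intervention survey will assess chronic stress (TICS, [22]), depression, anxiety, and stress (DASS, [23]) as well as trait rumination". State mood and state rumination "will be repeatedly administered at post-baseline, post-stress, and post-relaxation as well as in the evening of testing"; the first two of those occasions precede relaxation. Under Who will be blinded {17a}, participants do not know their arm until relaxation starts, so knowledge of the arm cannot have influenced their answers on any of these measures.

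**Analysis.** Item {20a} plans: "To test the effects of time (within-subject factor), group (between-subject factor), and the time by group interaction, repeated measures ANOVAs will be performed". It adds: "Additional two sample *t* tests will evaluate the group differences at relaxation and post-relaxation". Neither includes a covariate. Item {20b} then enters three covariates into those models, with an exploratory purpose: "To explore if the current stress level, trait mindfulness, and trait self-efficacy impact the success of the applied relaxation method". It closes with: "No additional subgroup or adjusted analyses are planned".

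**The concern.** For outcomes also measured before relaxation, the time by group interaction compares changes within people, so stable personal differences cancel. Post-event processing has two measurements, both after relaxation. Its interaction shows only whether the arms drift apart between the end of relaxation and the evening. Any overall effect of the relaxation method must appear in the group main effect or the t test, and there a person's habitual tendency to ruminate is part of the error term.

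A covariate that predicts the outcome would remove some of that error at almost no cost. Trait rumination is an obvious candidate and is already collected, yet it enters no stated model, and the last sentence of {20b} closes the list. At stake are a wider interval than the collected data may allow and, in any single trial, a chance imbalance in trait rumination that is left unadjusted.

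**Working it through.** **The plan's own figure.** Sample size {14} gives 88 for 80% success in both groups, a margin of 25 points and 90% power. Per arm: (1.645 + 1.282)² × 2 × 0.8 × 0.2 / 0.25² = 43.9, so 44, or 88 in total. This reproduces with one-sided alpha 0.05 (one-sided 0.025 would give 108). It concerns a binary success criterion and says nothing about the precision for post-event processing.

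**Inputs.** 50 per arm (100 recruited, 1:1). The correlation r between trait rumination and post-event processing is not in the protocol and is varied from 0 to 0.6. Results are in SD units of the quantity compared between arms. The two-sided 5% level and the illustrative true difference of 0.5 SD are assumptions made here.

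**Formulas.**
- Unadjusted 95% half-width: t(98) × √(2/50) = 1.984 × 0.200 = 0.397 SD.
- Adjusted for one covariate: t(97) × √(2/50) × √(1 − r²) × √(1 + 1/96). The last factor, 1.005, charges for estimating the slope.
- Example, r = 0.3: 1.985 × 0.200 × 0.954 × 1.005 = 0.381 SD.
- Example, r = 0.5: 1.985 × 0.200 × 0.866 × 1.005 = 0.346 SD.

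| r (assumed) | SE ratio | 95% half-width (SD) | Difference detectable with 80% power (SD) | Power at 0.5 SD |
|---|---|---|---|---|
| unadjusted | 1.000 | 0.397 | 0.566 | 69.7% |
| 0.1 | 1.000 | 0.397 | 0.566 | 69.7% |
| 0.2 | 0.985 | 0.391 | 0.557 | 71.0% |
| 0.3 | 0.959 | 0.381 | 0.543 | 73.3% |
| 0.4 | 0.921 | 0.366 | 0.521 | 76.6% |
| 0.5 | 0.871 | 0.346 | 0.493 | 81.1% |
| 0.6 | 0.804 | 0.319 | 0.455 | 86.8% |

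With 44 per arm the pattern is the same: 0.424 SD unadjusted, 0.407 at r = 0.3 and 0.369 at r = 0.5.

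**Chance imbalance.** The difference between arms in mean trait rumination has standard deviation √(2/50) = 0.20 SD, so about one trial in twenty exceeds 0.39 SD. At r = 0.5 such an imbalance moves the observed outcome difference by 0.5 × 0.39 ≈ 0.2 SD. The unadjusted interval already allows for this on average over randomisations; adjustment removes it in the trial at hand.

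**The case against.** The strongest reply is that this is a preference and not an error. Comparing randomised arms without adjustment is valid, and a short covariate list with a closing sentence is a sound guard against choosing covariates after seeing the data. Post-event processing is secondary, and no sample size claim depends on it. All of this stands and limits the weight of the point. It does not remove it, because the list is fixed in the text and leaves out a related measure that is already collected.

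Four stronger readings are tempting, and the protocol does not support them.
- *The plan forbids adjusted analyses.* It excludes only those beyond the three named covariates, which enter the repeated measures models. Because {20a} covers secondary outcomes, an exploratory covariate version for post-event processing already exists. Against that version, the gain depends on the correlation remaining after those three covariates and may be smaller than tabulated.
- *Trait rumination is the best available covariate.* State rumination after the stress task also precedes relaxation and follows the event being processed. It is at least as plausible, and nothing in the protocol ranks the two.
- *Between-person noise affects the whole analysis.* It affects the group main effect and the t tests. It drops out of the time and interaction tests. For the same reason there is little case for adding trait rumination to the state rumination model: that outcome has its own pre-relaxation values, and no gain has been shown for it.
- *The loss is large.* Large gains need r near 0.5 or 0.6, and the protocol offers no evidence for such values.

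**Conclusion.** The point holds as a minor one about precision. Post-event processing has no pre-relaxation value, and its main analysis uses neither rumination measure taken beforehand. The unadjusted comparison is unbiased and the primary stress and relaxation ratings are untouched.

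The size rests entirely on an unstated correlation: nothing is gained at r = 0.1, about 1.5% of the standard error at 0.2, about 4% at 0.3 and about 13% at 0.5. These figures assume 50 per arm, complete data, a linear relation and comparison with no covariate at all. The change is worthwhile if it can be made cleanly, but no conclusion of the trial depends on it.

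**What to change.** Keep the closing sentence of {20b}, since deleting it would remove the guard against further unplanned analyses for every outcome. Add one exception to it:

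> …, except that the group comparison of post-event processing (after relaxation and evening) will be adjusted by ANCOVA for trait rumination (RSQ, t1), with the unadjusted result also reported.

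Leave the state rumination model as it is. In the same edit, align the t4 and t5 labels for the first post-event processing assessment in Table 1 and Outcomes {12}.

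Timing matters. Trial status says recruitment ended in May 2021, and {21b} plans an analysis at N = 50 using the methods of {20a}. Date the change before the analyst is unblinded for the statistical tests ({17a}, {17b}). If that has already happened, including through the interim analysis, label the adjusted result post hoc.

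The cost is one degree of freedom and no new data; missing survey values fall under the multiple imputation planned in {20c}. The downside is little or no gain if r is 0.2 or less.

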**Fig. 1 Fig1:**

Procedure for laboratory testing session. Time points t1 to t5 from the schedule of enrollment are given as orientation. Time point t6 will be collected in the evening of the laboratory testing and is not included here. ECG, electrocardiogram; GSR, galvanic skin conductance response; Igroup, questionnaire on experienced presence in the VR; MAAS, Mindful Attention and Awareness Scale; MDBF, Mood State Questionnaire; PEPR, post-event processing; PSS-10, Perceived Stress Scale; RSQs, Response Style Questionnaire – state rumination; SWE, Self-Efficacy Questionnaire

##### Virtual reality setup

The multi-sensory VR was developed in cooperation with the Faculty of Media at the University of Applied Sciences in Düsseldorf, the chair of Ubiquitous Design/Experience and Interaction at the University of Siegen, the Department of Clinical Psychology of the University of Siegen, and industrial cooperation partners (LAVAlabs Moving Images GmbH & Co. KG, Düsseldorf; Medisana Space Technologies GmbH, Düsseldorf; tro GmbH, Düsseldorf; IOX GmbH, Düsseldorf). The VR includes visual, acoustic, and haptic features and is accompanied by a relaxing narrative. The VR environment comprises a landscape with fields and trees. At the beginning of the scene, the landscape is shown during the night. Participants will be able to see stars in the sky if they turn their heads upwards. During the course of the 14-min relaxation, sunrise is simulated with colors of the landscape changing from dark via orange sunrise to daylight. In front of the landscape an airy, blue sphere depicts a pattern of respiration by increasing for inhalation and shrinking for exhalation. See Fig. 2 for an illustration of the VR environment.

**Fig. 2 Fig2:**
[figure not shown]
Illustration of the VR environment. Beginning during night and ending during daylight. The blue sphere changes in size for the intervention on respiration increasing in size for inhalation and shrinking for exhalation

The VR will be presented using the HTC Vive pro HMD with a resolution of 2880 × 1600 pixels and a refresh rate of 90 Hz (HTC Corporation, ViveTM). The HTC Vive infrared sensor will be used to transfer participants’ head movements to the VR, thereby enhancing immersion. The VR is implemented using the Unity3D engine, which applies the C# language. A Nexus-10 MKII device (Mind Media, Herten, The Netherlands) will be used to continuously monitor the participant’s respiratory rate via a respiration belt tied around the chest.

During the first part of the VR intervention, the participant will have the possibility to familiarize with the VR environment, to listen to the introduction by the narrator, and to observe one’s own respiration. The sphere will not change in size and thus not reflect any respiratory pattern. During the second part of relaxation, starting with the fourth minute of the VR intervention, the blue sphere will increase in size for inhalation and shrink for exhalation. The respiratory rate simulated by the blue sphere will be adapted to the participant’s respiratory rate and slowed down to guide the participant’s respiration. This will be accomplished using a mapping algorithm. To calculate the decelerated respiratory rate for each participant, the duration of the participant’s respiratory cycles will be assessed during the first part and divided by two to approximate the duration of inhalation and exhalation. The duration of inhalation and exhalation will then each be mapped from values between 0 and 9 s to values between 4 and 9.5 s. This results in higher initial respiratory rates being more affected by the deceleration than lower initial respiratory rates. To achieve a longer exhalation than inhalation, 3 s is added to the computed exhalation duration. During the third part of the VR intervention, after 6 min, the user will be requested to hold the breath for 2 s following each inhalation and to exhale long and deeply.

Via headphones, participants will listen to calming music and nature sounds. In addition, a narrator will give instructions on relaxation and respiration. During the relaxation phase, participants will be seated on a cantilever chair with a massage mat (Medisana Space Technologies GmbH, Düsseldorf) placed on its surface. The massage mat will be automatically triggered by the Unity3D engine at the start of the VR. Pressure will be circularly applied to the back for a massage. In addition, heating elements will spread warmth to the back during massage. At the completion of the VR, the mat will strike down the back. As an additional feature, participants will be asked to place a custom-made pillow in their lap that responds synchronously to the increasing size of the blue sphere representing inhalation. Vibrations will start at inhalation onset, increase to a maximum and then decrease until the peak of inhalation. No vibrations will be given during the shrinking sphere representing exhalation.

